### **5.3 Contraindications for the 2nd dose**

Subjects who meet any of the following criteria cannot have the 2nd dose of the IP and will be treated in accordance with section 5.4 ‘criteria for subject discontinuation and withdrawal’.

- 1) The subject meets any of the criteria below after the 1st dose of the IP based on which the subject is ineligible for the 2nd dose in the opinion of the investigator.
  - ① COVID-19 positive based on RT-PCR diagnostic testing or SARS-CoV-2 infection positive based on antibody testing
  - ② Requiring prohibited drugs
  - ③ Development of thrombocytopenia or other coagulation disorders
- 2) Anaphylaxis or unexpected generalized hypersensitivity reaction after the 1st dose of the IP
- 3) SAEs relate to the IP
- 4) Pregnancy
- 5) Other clinically significant condition due to which the subject is ineligible for the 2nd dose in the opinion of the investigator

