## **1. Introduction**

### **1.1 Background of study**

Severe acute respiratory syndrome coronavirus 2 (SARS-CoV-2) is the pathogen of Coronavirus Disease-19 (COVID-19) that may result in acute respiratory distress syndrome in children and adults. SARS-CoV-2 is associated with a variety of signs and symptoms ranging from asymptomatic to mild symptoms such as fever, chills, cough, respiratory distress, fatigue, myalgia, headache, ageusia, anosmia, pharyngolaryngitis, nausea, vomiting, and diarrhea to severe diseases such as pneumonia and sepsis. Starting in China in December 2019, the novel virus has been fast spreading across the globe, within 3 months resulting in 113,702 infected cases and around 4,000 deaths in 114 countries as of 10 Mar 2020, which led to the declaration of COVID-19 pandemic by the World Health Organization as of 11 Mar 2020. Vaccines are considered to be the most effective tool to end COVID-19 by vaccination-induced herd immunity. Efforts to develop COVID-19 vaccine candidates by many developers and organizations are ongoing.

Developed by EuBiologics Co., Ltd. to prevent COVID-19, EuCorVac-19 is a recombinant protein vaccine in which a receptor-binding domain (RBD) antigen is bound to liposomes consisting of E. coli produced Monophosphoryl Lipid A (EcML), Cobalt-Porphyrin-Phospholipid (CoPoP), Dipalmitoylphosphatidylcholine (DOPC) and cholesterol.

EuCorVac-19 was found to have sufficient immunogenicity and safety in animal studies including efficacy, safety pharmacology, toxicity, genetic toxicity, and distribution studies. In the efficacy study with EuCorVac-19, titers of both anti-RBD Immunoglobulin G (IgG) and neutralizing antibodies increased more than 10 folds after the 2nd dose in comparison with the 1st dose, indicating an increase in efficacy in proportion to dose. Results from the analysis of cellular immunity 2 weeks after the 2nd dose showed that IFN $\gamma$ , TNF- $\alpha$ , IL-2, and IL-4 levels tended to increase in proportion to dose, with a significant rise observed particularly in high-dose groups. Given Th1 biased immune response, antibody-dependent adverse events (AEs) are unlikely in humans.

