#### **4.1.2 Immunogenicity assessment**

Subject has to keep fasting (prohibition of food or beverage except water for 8 hours) before blood

sample collection for immunogenicity assessment. At least 28mL at pre-dose (Visit 2), at least 25mL on Day 21 after the 1st dose (Visit 5), at least 25mL on Day 21 after the 2nd dose (Visit 8), and at least 5mL on Week 26 (Visit 10), and Week 52 (Visit 11) after the 2nd dose of blood samples will be collected. Each of 20mL of blood samples collected at Visit 2, Visit 5 and Visit 8 will be stored in appropriate container and at appropriate temperature to be sent to the central laboratory (Vaccine/Bio Research Institute at the Catholic University of Korea, College of Medicine).

Besides, blood samples collected at other visits will be stored at room temperature for at least 30 minutes to 2 hours for blood coagulation reaction. After the coagulation, blood will be separated to achieve serum by a centrifuge. Separated serum will be split into several and appropriate containers and stored at appropriate temperature before sending to the central laboratory (International Vaccine Institute).

Humoral immunity will be tested by the International Vaccine Institute, and cellular immunity will be tested by the Vaccine/Bio Research Institute at the Catholic University of Korea, College of Medicine. Samples for immunogenicity testing will be sent to the central laboratory designated for each test for collective measurement and analysis.

- **Humoral immunity testing (total volume of blood to be collected: at least 8 mL pre-dose (Visit 2), at least 5 mL at other visits)**

- 1) Antigen protein-specific antibody test using ELISA: approximately 3 mL of blood
  - To assess the titer of the antibody specifically binding to the RBD of the spike protein induced by the IP in the serum of the subject treated with the IP.

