  - After coating the recombinant protein containing antigen protein receptor binding domain(RBD) in 96-well plate for ELISA, each well will be washed with washing solution and then filled with blocking buffer and stored at room temperature. Then blocking buffer will be removed, each well will be washed with washing solution once, and serum of each study subjects will undergo serial dilution. Blocking buffer will be removed from the plate, washed with washing solution, and then HRP conjugated anti human IgG will be added to each well and the plate will be washed. TMB substrate will be added, and TMB stop solution will be added depends on color development, and absorbance will be measured.
  - Geometric mean titer (GMT) and geometric mean fold rise (GMFR) will be calculated for antigen protein-specific IgG on the relevant day versus pre-dose of the IP. A serum is determined positive when mean absorbance in the serum of the same dilution rate on

the relevant day is greater than “mean absorbance +3x standard deviation (SD)” in the pre-dose serum; antibody titer is defined as the reciprocal number of the value with the greatest dilution rate.

- Seroconversion is defined as a  $\geq 4$ -fold increase in GMT post-dose of the IP from pre-dose, which is  $\geq 4$ -fold of GMFR.

2) Neutralizing antibody test using FRNT (Wild-type SARS-CoV-2): approximately 2 mL of blood

- To measure the amount of SARS-CoV-2-specific neutralizing antibodies induced by the vaccine, a focus reduction neutralization test (FRNT) will be performed using wild-type SARS-CoV-2.
- Vero cells will be cultured to 96 well plate by seeding, and serum of study subjects which was diluted consecutively from 1/20 to 2-fold will be mixed with SARS-CoV-2 and induced reaction. Reacted SARS-CoV-2-serum mixture will be cultured by seeding into vero cell, then cell culture media will be removed from mixture, and cells will be fixed with formalin and antibody in cells will be stained with methanol. The fixed cells will be treated with SARS-CoV-2 nucleocapsid protein (NP) specific antibody, and the amount of foci which are created by color development will be counted by CTL reader.

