#### **4.1.3.6 COVID-19 diagnostic test and antibody test**

At the screening visit and Visit 2, subjects will be tested for COVID-19 for the inclusion/exclusion criteria checking. Using upper respiratory tract sampling (oropharyngeal/ nasopharyngeal swab) and lower respiratory tract sampling (an additional sputum test will be performed in the presence of symptoms such as cough and sputum), reverse transcription-polymerase chain reaction (RT-PCR) diagnostic test and COVID-19 antibody test (positivity to IgM and IgG; 20 µL of blood) will be performed to determine past and/or current COVID-19 infection. During screening, antibody test will be performed as clinical laboratory test and at Visit 2, the test may be performed by the institution or the COVID-19 diagnostic kit provided by the sponsor.

Subjects who have the following symptoms of COVID-19 infection after randomization should follow the guideline on COVID-19 by ‘Central Disease Control Headquarters · Central Disaster Management. Headquarters’ and inform the symptoms to the investigator. As much as possible, the subjects should be instructed to visit the institution and have medical treatment and diagnosis.

- $\geq 37.5^{\circ}\text{C}$  fever or chills, fatigue, myalgia or body aching, headache, sore throat, anosmia and ageusia, nasal obstruction or nasal discharge, nausea or vomiting, diarrhea, cough, respiratory distress or respiratory disturbance

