**4.2.12 Unscheduled visits**

Besides scheduled visits, additional visits may be conducted any time upon the request of subjects or their representatives or whenever deemed necessary by the investigator. The investigator will remind the subjects of this during their regular study visits and instruct them to immediately contact the investigator in the event of AEs. Unscheduled visits should not affect the schedules of regular visits. During unscheduled visits, tests can be done as necessary at the discretion of the investigator.

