### **5.2 Exclusion criteria**

Individuals who meet any of the criteria described below will be excluded from enrollment.

- 1) COVID-19 positive based on RT-PCR using upper respiratory tract (oropharyngeal, nasopharyngeal) or lower respiratory tract (sputum) sampling or COVID-19 antibody (IgM and/or IgG) positive
- 2) History of SARS-CoV, MERS-CoV or SARS-CoV-2 infection
- 3) Increased risk of exposure to SARS-CoV-2 (e.g., healthcare workers in direct contact with patients with COVID-19)
- 4) History of vaccination against SARS-CoV, MERS-CoV, or SARS-CoV-2
- 5) Immune system disorders including immunodeficiency disease
- 6) Planned blood donation or transfusion during the study period
- 7) Planned administration of other vaccines from 4 weeks before the 1st dose to 4 weeks after the 2nd dose of the IP
- 8) Height and/or weight measurements at screening:
  - ① Body weight <40 kg or > 100 kg
  - ② Body mass index <18 kg/m^2 or > 30 kg/m^2
- 9) Clinically significant abnormalities in clinical laboratory test, ECGs and chest X-ray during screening in the opinion of the investigator (e.g., Wolff-Parkinson-White syndrome)

- 10) Any planned surgery during the study period
- 11) Fever ( $\geq 37.5^{\circ}\text{C}$ ) within 3 days prior to screening or serious acute (acute fever, cough, respiratory distress, chills, myalgia, headache, sore throat, anosmia, or ageusia) or chronic infection within 7 days prior to screening (requiring systemic antibiotics or antivirals)
- 12) Evidence or history of serious acute, chronic, or progressive disease (e.g., cancer, diabetes mellitus, chronic pulmonary disease, acquired immune deficiency syndrome (AIDS), blood dyscrasias, or immune system, urinary system, mental, musculoskeletal system, cardiovascular system, respiratory system, endocrine, nervous system, hepatobiliary system, renal disorders, etc.) which, in the opinion of the investigator, makes the individual ineligible for the study
- 13) Positive serum tests during screening [type B hepatitis, human immunodeficiency virus (HIV), type C hepatitis]
- 14) History of treatment with antipsychotics or opioid analgesic dependence within 6 months prior to IP dosing
- 15) History of severe allergic reactions (e.g., anaphylaxis, Guillain-Barré Syndrome) or severe hypersensitivity reactions to the IP or any of its components

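### Section 5.3 lets an antibody test of unstated antigen stand in for RT-PCR as proof of infection after dose 1, although the vaccine is meant to raise anti-RBD antibody by then

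*Protocol*

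**What the plan says.** Section 5.3 of the Protocol lists the conditions under which a subject cannot have dose 2. Item 1) applies after dose 1 where the investigator judges the subject ineligible, and its first entry is "COVID-19 positive based on RT-PCR diagnostic testing or SARS-CoV-2 infection positive based on antibody testing". Section 5.4 then treats the subject as a possible discontinuation, after discussion between investigator and sponsor.

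The product is described in Section 1.1 as "a recombinant protein vaccine in which a receptor-binding domain (RBD) antigen is bound to liposomes", and the composition tables in Section 6.1.1 show RBD as the sole active ingredient. The purpose of the ELISA in Section 4.1.2 begins "To assess the titer of the antibody specifically binding to the RBD of the spike protein induced by the IP". Section 7.2.2 measures that antibody, and seroconversion to it, at Visit 5.

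The clinical COVID-19 antibody test is described in Section 4.1.3.6 and in note 4 to the Schedule of Assessments. It is an IgM/IgG test on 20 µL of blood, used together with RT-PCR "to determine past and/or current COVID-19 infection", and no target antigen is given. On timing, Section 4.1.3.6 says "At the screening visit and Visit 2, subjects will be tested for COVID-19 for the inclusion/exclusion criteria checking". Neither Visit 4 nor Visit 5 lists a COVID-19 test. Outside the schedule, Sections 4.1.3.6 and 8.2 send symptomatic subjects for assessment, and Section 4.2.12 says "During unscheduled visits, tests can be done as necessary at the discretion of the investigator".

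**The concern.** Before vaccination an antibody test is reasonable evidence of past infection, and the entry criterion in Section 5.2 uses it in that way: "COVID-19 antibody (IgM and/or IgG) positive". After dose 1 of an RBD vaccine this no longer holds unless the test targets an antigen that the vaccine does not contain. The protocol carries the antibody route over to the dose-2 decision without that condition. At Visit 5 the same kind of signal is therefore an immunogenicity outcome under Section 7.2.2 and possible grounds for withholding dose 2 under Section 5.3.

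At stake is the handling of individual vaccinees. A subject whose positive result reflects the intended response could be denied dose 2. That subject would go to Visit 9 procedures, which include no immunogenicity sample, and so would probably have no Visit 8 titre. Section 7.3.1 lists a missing Visit 8 test among the deviations that may lead to exclusion from the per-protocol set, which is the primary set for immunogenicity. Exclusion is proper for someone who had one dose; the harm is that dose 2 was withheld for the wrong reason. Vaccine-induced false positives cannot arise in saline recipients.

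**Working it through.** **What the criterion requires.**

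- Section 5.2, exclusion 1 (before dose 1): a bare antibody-positive result is enough. The subject is unvaccinated, so this is sound.
- Section 5.3, item 1)-① (after dose 1): infection must be shown, but antibody testing is accepted as an alternative to RT-PCR. The word infection states the target; it does not supply a method that reaches it.
- Section 4.1.3.6 and Schedule note 4: IgM/IgG, antigen unstated. At Visit 2 the test may come from the institution or from a sponsor-supplied kit, so no single assay is fixed.
- Section 4.1.2: "SARS-CoV-2 nucleocapsid protein (NP) specific antibody" appears as the staining reagent in the neutralization assay. It is not a serology test on subjects and does not fill the gap.

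**Can another stated means resolve a positive result?** RT-PCR can confirm current infection. A negative RT-PCR cannot exclude a cleared infection, and because the two methods are alternatives it does not cancel a positive antibody result. Under Section 6.5, investigators outside the designated unblinded personnel stay blinded. Unblinding is reserved for medical emergencies and ends the subject's participation.

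**When can the rule act?** Dose 2 is due 21 days after dose 1 with a window of +5, so the interval is 21 to 21 + 5 = 26 days. The Schedule of Assessments places no COVID-19 test in it. Only symptom-driven tests (Sections 4.1.3.6, 8.2) or unscheduled tests (Section 4.2.12) can trigger the rule.

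**Plan's own figures (Section 7.1.1.2), reproduced.** Enrolled = evaluable / (1 − 0.15):

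- 85 / 0.85 = 100
- 25 / 0.85 = 29.4, rounded up to 30
- 195 / 0.85 = 229.4, rounded up to 230

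These agree with the protocol and are not disputed.

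**Loss per case in a Part B vaccine arm.** 1 / 85 = 1.2% of planned evaluable subjects, if evaluable is read as per-protocol.

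**What would exhaust the drop-out allowance.** 100 − 85 = 15 subjects, that is 15 / 100 = 15% of an arm misclassified with no other drop-outs. Let q be the share of the arm given an antibody test between doses and s the share of those tested who are positive through vaccination, and suppose every positive is acted on. The number withheld is 100 × q × s, and it reaches 15 when q × s = 0.15. The protocol gives neither q nor s. For assumed values:

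| s (assumed) | q needed for 15 withheld |
|---|---|
| 0.9 | 0.15 / 0.9 = 16.7% |
| 0.3 | 0.15 / 0.3 = 50% |

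If q is zero, or the kit does not detect spike/RBD antibody, the number withheld is zero. These values only show what would be needed; they are not estimates.

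**Which analysis sets keep the subject.**

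- Safety set: kept, since one dose suffices.
- Part A target of 25 per dose group (Section 7.1.1.1): kept, since it counts subjects dosed at least once.
- FAS: kept if the Visit 5 sample was drawn; Section 4.2.5 lists that sample ahead of the contraindication check.
- PPS: may be excluded, because the Visit 8 titre is missing.

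**The case against.** The strongest reply is that harm depends on several things the protocol does not establish. The kit must react to spike/RBD antibody; its specification may sit in a laboratory document not at hand, and with a nucleocapsid kit the problem disappears. Someone must choose to run serology between doses, and no section prescribes it, even for symptomatic subjects. The investigator must then regard the result as infection, knowing that an RBD vaccine may have been given. RT-PCR is named in the same clause. In a first-in-human trial with enhanced disease among the adverse events of special interest, withholding dose 2 on suspected infection is also a defensible caution.

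All of this stands as a limit on size. It does not make the criterion sound. Where the rule does act, it accepts a method that may be unable to answer its own question, and a blinded investigator cannot tell vaccine response from a cleared infection on an RBD-reactive result. Caution about true infection is kept if the method is corrected.

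Three stronger readings are tempting, and the protocol does not support them:

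- That vaccine responders would routinely be barred from dose 2. No test is scheduled between doses and the investigator's judgement intervenes.
- That each case costs 1 of 15 vaccinees (6.7%) against the Part A target. That target counts subjects with at least one dose, so the subject remains in it.
- That removing antibody-positive subjects biases GMT or SCR. This would need the number misclassified and a link between kit positivity after dose 1 and titre after dose 2. The protocol gives neither.

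**Conclusion.** The point holds as a minor design weakness in Section 5.3. After dose 1 the criterion accepts antibody testing of unstated antigen as sufficient proof of infection, in a trial of a vaccine meant to raise anti-RBD antibody. Any harm assumes a spike/RBD-reactive kit, a discretionary or symptom-driven test within the 21 to 26 days between doses, and an investigator who accepts the result as infection. How many subjects meet all three is unknown and may be none, and a material shortfall in evaluable numbers is unlikely. The trial tests no hypothesis and has no powered sample size (Section 7.1.2), so there is no power to lose. What remains is a rule that could withhold dose 2 from an individual for responding as intended, and that is cheap to correct.

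**What to change.** Amend Section 5.3, item 1)-①, so that after dose 1 SARS-CoV-2 infection is established by RT-PCR, or by antibody to an antigen not contained in EuCorVac-19 (for example nucleocapsid). Add that a spike/RBD antibody result is not used for the dose-2 decision. Whether a truly infected subject receives dose 2 stays as the sponsor has defined it.

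The cost is one or two sentences, with no added visits or scheduled samples. The downside is that a past infection that is RT-PCR negative when tested will be detected only if a nucleocapsid assay is used.

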### **5.4 Criteria for subject discontinuation and withdrawal**

Those who are randomized but cannot participate in the study for the entire period for any reason will be classified as dropouts. Subjects may choose to discontinue the study at any time for any reason by requesting withdrawal. Or subjects may also be discontinued at any time for safety, behavioral, or administrative reasons at the discretion of the investigator or the sponsor. The investigator should ask about reasons for withdrawal and ask the subject to return for the last visit. If applicable, the investigator should make every effort to follow up on unresolved AEs.

For the following reasons, subjects may ask for withdrawal or may be discontinued or withdrawn

upon discussion with the investigator and the sponsor. In this case, the reasons and actions taken for the discontinuation and withdrawal should be recorded on the relevant document as well as on the CRF:

- ① The subject or his/her representative withdraws informed consent.
- ② Violation of the inclusion/exclusion criteria is identified during the course of the study.
- ③ The subject corresponds to exclusion criteria for 2nd dose.
- ④ The subject or his/her representative wants to discontinue the study due to unsatisfactory therapeutic effects during the study period.
- ⑤ The subject does not comply with instructions of the principal investigator or the sub-investigator.
- ⑥ Lost to follow-up.
- ⑦ The subject becomes pregnant during the study period.
- ⑧ Study participation is inappropriate for other reasons based on the judgment of the sponsor or the investigator

If possible, subjects who are withdrawn after Visit 2 and before Visit 9 (end of main study visit) will return to the institution for Visit 9 procedures. If possible, those who are withdrawn after Visit 9 will return to the institution for Visit 11 (end of follow-up visit) procedures except for blood sampling for immunogenicity testing. For safety follow-ups for dropouts, if consent is obtained from the subject, telephone visits will be conducted by a trained sub-investigator who will call the subject at the time points of Visit 10 (Week 26 after the 2nd dose of the IP) and Visit 11 (Week 52 after the 2nd dose of the IP) for SADRs and AESIs.

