- 11) If possible, subjects who are withdrawn from the study will visit the institution for required procedures. Those who are withdrawn prior to Visit 9 (end of main study visit) will perform Visit 9 procedures. Those who are withdrawn after Visit 9 will perform Visit 11 procedures (end of follow-up visit) except for blood sampling for immunogenicity testing. If consent is obtained from the subject, telephone visits will be conducted by a trained sub-investigator who will call the subject at the time points of Visit 10 (Week 26 after the 2nd dose of the IP) and Visit 11 (Week 52 after the 2nd dose of the IP) for serious ADRs and AESIs. Subject who has not performed administration of 2nd dose investigational product will conduct Visit 10 and Visit 11 on the basis of scheduled date of 2nd dose administration.
- 12) Concomitant drugs administered for SAEs and AESIs will be collected.
- 13) Status of SAEs and AESIs will be checked. In the event of an AESI, additional tests may be conducted as necessary at the discretion of the investigator, and if necessary, the DSMB may meet to review the case for status of ADR and enhanced disease.

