#### **4.2.9 Visit 9 (end of main study visit, 28 + 7 days after the 2nd dose)**

This visit will take place on Day 28 after the 2nd dose of the IP. Procedures to be carried out during this visit are as follows. The following procedures are also applicable to those who discontinue the study prior to Visit 9. Subsequently, if consent is obtained from the subject, telephone visits will be conducted by a trained sub-investigator who will call the subject at the time points of Visit 10 (Week 26 after the 2nd dose of the IP) and Visit 11 (Week 52 after the 2nd dose of the IP) for serious ADRs (SADRs) and AEs of special interest (AESIs).

- Any change from the last visit in concomitant medications will be checked.
- The subject diary will be retrieved for status and details of AEs.
- Vital signs will be measured.
- Physical examination will be conducted.
- Clinical laboratory tests (hematology, blood chemistry, urinalysis) will be performed.
- Pregnancy test will be performed for women of childbearing potential.
- The next visit day will be scheduled.

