**4.2.11 Visit 11 (end of follow-up visit, 52 ± 4 weeks after the 2nd dose)**

As the final study visit, this visit will take place at Week 52 after the 2nd dose of the IP. Those who are withdrawn after Visit 9 will perform the following procedures except for blood sampling for immunogenicity testing, and if consent is obtained from the subject, telephone visits may be conducted by a trained sub-investigator who will call the subject at the time points of Visit 10 (Week 26 after the 2nd dose of the IP) and Visit 11 (Week 52 after the 2nd dose of the IP) for SAEs and AESIs.

- Any SAEs and AESIs since last visit will be checked. If the subject experienced SAEs and AESIs, concomitant medications given for these events will also be documented.
- Vital signs will be measured.
- Pregnancy test will be performed for women of childbearing potential.
- A blood sample will be collected for immunogenicity testing.

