## 7.2 Endpoints

### 7.2.1 Safety endpoints

- AEs
  - ① Immediate AEs occurring within 30 minutes after each IP dosing
  - ② Solicited local and systemic AEs occurring for 7 days (Day 0~ Day 6) after each IP dosing
    - ✓ Local AEs : pain, tenderness, erythema/redness, induration/swelling, itchiness
    - ✓ Systemic AEs : fever, fatigue/malaise, chills/rigors, headache, myalgia, joint pain, diarrhea, vomiting, abdominal pain, mucocutaneous reaction/rash, cough, acute bronchospasm, respiratory distress
  - ③ Unsolicited AEs occurring within 28 days after the last IP dosing
  - ④ SAEs occurring within 52 weeks after the last IP dosing
  - ⑤ AESIs occurring within 52 weeks after the last IP dosing
- Clinical laboratory tests (hematology/blood chemistry, urinalysis)
- Vital signs
- Physical examination

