### 7.3 Statistical analysis plan

#### 7.3.1 Analysis sets

Safety data obtained from the study subjects will primarily be analyzed in the safety set while immunogenicity data will be analyzed primarily in the per-protocol set (PPS) and additionally in the full analysis set (FAS).

Analysis sets are defined as follows.

(1) Safety Set:

Includes all subjects who had at least one dose of the IP.

(2) FAS (Full Analysis Set):

Includes all subjects who had at least one dose of the IP, pre-dose immunogenicity data and at least one post-dose immunogenicity endpoint data available. Hence, the number of subjects may vary depending on the number of immunogenicity endpoints.

(3) PPS (Per-Protocol Set):

Includes all subjects in the FAS who completed the study through to Visit 9 (end of main study visit) according to the protocol. In the follow-up analysis, those who completed the study through to the end of follow-up visit (Visit 11) will separately be analyzed. Subjects with any of the following protocol deviations may be excluded from the PPS.

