#### **7.3.4.1 Adverse events**

Summary descriptions will be provided as below for details of treatment emergent AEs (TEAEs).

Frequency, incidence, and number of events will be presented for solicited local and systemic AEs observed for 7 days (Day 0~Day 6) after each IP dosing, immediate AEs (anaphylaxis related) occurring within 30 minutes after each IP dosing, and unsolicited AEs occurring within 28 days after the last IP dosing. By treatment group, type of AEs will be classified by severity, causal relationship, outcome, etc., and frequency, incidence, and number of events will be presented by category.

Additionally, frequency, incidence, and number of events will be presented for SAEs and AESIs collected within 52 weeks after the 2nd dose of the IP.

All AEs except for solicited local and systemic AEs will be classified by system organ class and preferred term of Medical Dictionary for Regulatory Activities.

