#### **(2) ADRs**

An ADR is any unfavorable and unintended event occurring at any dose of the IP for which causal relationship to the IP cannot be ruled out.

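### Footnote 11, 4.2.9 and 5.4 limit the Week 26 and Week 52 calls to dropouts to serious ADRs and AESIs, in conflict with 4.2.11 and with the 52-week all-SAE endpoint

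*Protocol*

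**What the plan says.** Four places in the protocol describe the telephone calls to dropouts at the Visit 10 and Visit 11 time points:

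- Schedule of Assessments, footnote 11, after dealing with withdrawal both before and after Visit 9: "for serious ADRs and AESIs".
- Section 4.2.9, for those who discontinue before Visit 9: "for serious ADRs (SADRs) and AEs of special interest (AESIs".
- Section 5.4, as safety follow-up of dropouts in general: "for SADRs and AESIs".
- Section 4.2.11, for those withdrawn after Visit 9: "for SAEs and AESIs".

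Section 8.1 gives SAEs and SADRs the same seriousness criteria. An SADR must also be an ADR, an event "for which causal relationship to the IP cannot be ruled out". SADRs are therefore the possibly related subset of SAEs.

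The safety endpoint in 7.2.1 is "SAEs occurring within 52 weeks after the last IP dosing". In 7.3.4.1, "frequency, incidence, and number of events will be presented for SAEs and AESIs collected within 52 weeks" after the second dose. The Safety Set in 7.3.1 "Includes all subjects who had at least one dose of the IP", and 7.3.6 rules out imputation. Section 8.2 collects SAEs from the first dose to Visit 11, and 8.4 has all of them reported over that period whether or not they are related.

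**The concern.** The endpoint counts every SAE in everyone dosed, yet most of the text on dropout calls asks only for serious events that pass a causality filter, plus AESIs. A dropout who has an unrelated serious event that is not on the AESI list stays in the denominator, but the scheduled call does not ask about that event. With no imputation, an event that was never asked about is tabulated as no event.

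Filtering by relatedness on the telephone also puts the causality judgement before the record. Section 8.3.2 (causal relationship) treats relatedness as an assessment made of an AE. If an event is never recorded because the caller thought it unrelated, that judgement cannot be reviewed later. Elsewhere the protocol narrows serious-event reporting to related events only after Visit 11 (8.2 and 8.4), so a narrower scope before Visit 11 is out of line with its own scheme.

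Safety is the primary objective of Part A and a secondary objective of Part B, in a first-in-human trial. An analysis plan could not repair this, because the question is what data are collected.

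**Working it through.** **Step 1. Which passages conflict, and for whom.**

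| Place | Dropouts covered | Serious events asked about |
|---|---|---|
| Footnote 11 | withdrawn before or after Visit 9 | serious ADRs |
| 5.4 | all | SADRs |
| 4.2.9 | withdrawn before Visit 9 | SADRs |
| 4.2.11 | withdrawn after Visit 9 | SAEs |

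- Withdrawn after Visit 9: footnote 11 and 5.4 say one thing and 4.2.11 another. This is a direct contradiction.
- Withdrawn before Visit 9: footnote 11, 4.2.9 and 5.4 agree with one another. The conflict is with 7.2.1 and 7.3.4.1 (all SAEs to 52 weeks) and with 8.2 and 8.4 (all SAEs to Visit 11).

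**Step 2. The plan's drop-out figure.** Section 7.1.1.2 allows 15% in Part B. Inflating by n/(1 − 0.15):

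- 85/0.85 = 100
- 25/0.85 = 29.4, rounded up to 30
- 195/0.85 = 229.4, rounded up to 230

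These reproduce the stated 100, 100, 30 and 230. At 15%, 0.15 × 230 = 34.5, so about 35 Part B subjects. The allowance is for availability for immune response analysis. It is used here only as a ceiling on the share followed by telephone.

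**Step 3. Size of the possible under-count.** Let d be the dropout share, f the share of 52-week SAE risk that falls in the telephone-only period, and r the share of SAEs judged related. If the narrow wording is followed literally and SAE risk is the same in dropouts as in others,

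relative under-count = d × f × (1 − r).

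The protocol gives no value for f, r or the SAE incidence. The assumed ranges are d = 5% to 15%, f = 0.5 to 1 and r = 0 to 0.5:

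- low end: 0.05 × 0.5 × (1 − 0.5) = 0.0125, or 1.25%
- high end: 0.15 × 1 × (1 − 0) = 0.15, or 15%

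**Step 4. In subjects, Part B (N = 230).**

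| Assumed SAE incidence | Expected subjects with an SAE | Missed, low end to high end |
|---|---|---|
| 1% | 2.3 | 0.03 to 0.35 |
| 3% | 6.9 | 0.09 to 1.03 |
| 5% | 11.5 | 0.14 to 1.7 |

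At 3%, the observed incidence would be 3% × (1 − 0.15) = 2.55% at worst and 3% × (1 − 0.0125) = 2.96% at best. AESIs are asked about in every version of the text, so SAEs that are also AESIs would reduce these losses further.

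**The case against.** The strongest reply is that the collection rules already settle the matter. Section 8.2 makes no exception for dropouts, and 8.4 has every SAE to Visit 11 reported regardless of relationship. To find a related serious event the caller must first hear of the event, and 8.4 then makes it reportable. This stands in part: a reader might infer that the SAE endpoint is bound to be under-counted, and the protocol does not show that. But 8.4 acts only on events that the investigator knows of, and the calls are how an investigator would learn of them.

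Other inferences also go further than the text allows:

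- **Three places contradict a fourth.** Section 4.2.9 and 4.2.11 cover different dropouts, so these two do not contradict each other. The direct contradiction is footnote 11 and 5.4 against 4.2.11. Subjects withdrawn after Visit 9 are also asked back, where possible, for Visit 11 procedures, which include a check of all SAEs.
- **Subjects barred from the second dose get the narrower follow-up.** They are routed through 5.4, but the last sentence of footnote 11 has subjects without the second dose carry out Visits 10 and 11 by its scheduled date. If that means full visits, all SAEs are checked. If it only times the calls, they are not. The text does not say which.
- **The vaccine-placebo comparison is biased.** Nothing in the protocol shows that withdrawal, or the share judged related, differs by arm. The SAE summary is descriptive, and 7.1.2 states that no hypothesis is tested.
- **Fifteen per cent is the expected loss.** It requires every dropout to leave at the start and every SAE to be unrelated, not an AESI and not learned of in any other way.

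**Conclusion.** The inconsistency holds. The protocol gives two scopes for the same calls in subjects withdrawn after Visit 9. In subjects withdrawn before Visit 9, it gives a scope narrower than its own endpoint and its own collection and reporting rules. The consequence is a risk of incomplete SAE ascertainment if sites follow the narrow wording; it is not a demonstrated bias.

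The effect is probably small: 1.25% to 15% relative, or about 0.1 to 1.0 of 6.9 expected Part B subjects with an SAE. This rests on the assumed ranges for d, f and r, an assumed 3% incidence, equal SAE risk in dropouts, and the 15% allowance taken as a ceiling. The change is still worth making, because it is cheap and an event that was not collected cannot be recovered at analysis.

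**What to change.** Reconcile the passages:

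1. In footnote 11, 4.2.9 and 5.4, have the calls ask about all SAEs and AESIs, as in 4.2.11, 7.2.1, 8.2 and 8.4. Assess relatedness after the event is recorded.
2. Align the strength of the instruction: 4.2.11 says the calls may take place, while the other three places say they will.
3. State whether the last sentence of footnote 11 gives subjects without the second dose full Visits 10 and 11, or only sets the dates of their calls.

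The cost is a wording change in a few places and in the call script. The calls are already planned, and no visit or blood sample is added by items 1 and 2. Some loss will remain because the calls depend on the dropout's consent. The report should therefore state how many dropouts in each arm were reached at Weeks 26 and 52.
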